## Abstract

**Background:** Age-related hearing loss (presbycusis) is a form of hearing loss in over 60-years-olds and has a negative impact on quality of life. Presbycusis is multifactorial and is predominately characterised with a loss of speech perception in noise. In the cochlea, auditory filters decompose broadband sound into a series of narrowband output signals, which contains two kinds of temporal information: slow changes in overall amplitude envelope (ENV) and faster variations in temporal fine structure (TFS). TFS is important for recognition of target speech in noise. The main aim of the study is to evaluate the effect of TFS rehabilitation training in participants over the age of 60 years with mild to moderate hearing loss.

**Methods:** A randomised clinical trial  conducted on 30 participants with mild (loss of 20-39dB HL) to moderate (40-69dB HL) hearing loss, aged between 60 and 75 years old. Participants with conductive hearing loss, abnormal middle ear pathology and central nervous system disease were excluded. Participants were selected randomly  to an intervention and control group with a 1:1 ratio. Rehabilitation for the intervention Group are 30-minute sessions three times a week for a total five weeks of vowel consonant vowel words that are used to eliminate ENV and keep only TFS. Word in noise test, binaural TFS test, and Speech, Spatial and Qualities of Hearing Scale scores are performed at the beginning and end of study to evaluate the effect of rehabilitation training.

**Conclusion: ** Life expectancy in the elderly has improved, leading to an increased prevalence of age-related diseases including presbycusis. A literature review highlighted that TFS damage is permanent; however, in this study we will attempt to prove that TFS training may lead to speech in noise perception improvement.

**Trial registration: **Registry of Clinical Trials,
IRCT2019625044006N1 (7
^th^ August 2019).

## Introduction

Presbycusis (age-related hearing loss) is one of the most common disorders worldwide
^1,
2^. The cause of presbycusis is multifactorial, including pathophysiological degeneration, extrinsic and intrinsic damage, genetic predisposition and comorbidities (conditions like diabetes, hypertension and stroke)
^3–
5^.

In cochlea high frequency sounds evoke greatest vibration of the basilar membrane at the base while lower frequency sounds evoke greatest vibration at the apex
^6–
9^. Sounds are decomposed to narrow band signals temporal envelope (ENV) and rapid oscillations temporal fine structure (TFS)
^9–
12^. The ENV frequency range is between 2–50 Hz. One of the most important tasks of ENV is to identify speech in quiet environments
^11,
12^. TFS frequency range is between 0.6–10 kHz
^13^, and TFS cues are important in perception of pitch, tone separation
^14^, and identify target speech in interfering sounds
^15^. Presbycusis is associated with loss of speech perception in noisy environments
^16^ and deterioration of the processing of TFS information
^14,
15,
17^.

Previous studies indicate that sensorineural hearing loss is associated with a reduction in speech recognition and is dependent on deterioration of TFS
^18^, showing the importance of TFS for listening with background sounds
^8^. Studies by Hopkins
*et al.* suggest that TFS is important to recognise the temporal dips in fluctuating background noise
^19,
20^. In an elderly population with high frequency hearing loss, even when absolute thresholds are within the normal range, the TFS can be damaged
^21^. It is speculated that TFS information is useful for separation of the target speech in background speech
^22^.

### Objectives

The main aim of the study is to evaluate the impact of special rehabilitation training based on TFS on improvement of speech in noise perception in an elderly population with mild to moderate hearing loss.

## Protocol

This is version 3 of the protocol. There is no plan for further trial modifications.

### Study overview

We conduct a randomised clinical trial of rehabilitation training on speech in noise perception performance on an elderly population with mild to moderate hearing loss at the Audiology Clinic of School of Rehabilitation Sciences, Iran University of Medical Sciences (Tehran, Iran). It is hypothesized that the inability to use TFS speech cues is the main cause of speech perception problem in noise in elderly individuals, and it is possible by designing appropriate rehabilitation exercises to reduce the difficulty of speech perception in noise.

The Medical Ethics Committee at the Iran University of Medical Sciences approved the registered study protocol (IR.IUMS>REC.1398.003). The study was registered on the Iranian Registry of Clinical Trials (registration number,
IRCT2019625044006N1), a Primary Registry in the World Health Organization Clinical Trials Registry Network.

The protocol does not involve complications for participants in the study. All participants were informed both verbally and in writing about the study procedure. Written consent to participants were obtained from the participants before the study start (see
*Extended data:* S1).

### Terminology used in this study

*Mild to moderate hearing loss:* auditory thresholds ≤25dB within the frequency<2000 Hz and 25–70 dB HL with frequency 2000–8000 Hz.

*TFS-LF test:* software designed by Hopkins and Moore in 2010. The test is originally based on measuring the interaural phase differences
^15^.

*Interaural phase difference (IPL):* lowest difference in the phase of the wave in each ear and dependent frequency sound waves and difference in time between ears
^15^.

*Signal to noise ratio (SNR):* ratio of the power of a signal (meaningful information) to the power of background noise (unwanted signal), expressed in decibels (dB). Larger numbers for signal characteristics mean better and more useful than unwanted noise information
^23^. In this study the signal-to-noise ratio levels were 0, 4, 8, 12, 16, 20, and 24 dB.

*Speech in noise score:* measured by Persian version of WIN test (PARWIN list), which is expressed as a percentage by performing a single syllable word test. The PARWIN test is a version of the Richard H. Wilson WIN test, in which the background noise in this test is baffled noise
^24^. PARWIN test is used to estimate SNR (50%) using Spearman Karber equation.

*Speech, Spatial and Qualities of Hearing Scale (SSQ) questionnaire:* used in previous studies in elderly individuals with communication disorders caused by hearing loss. From the original version of the SSQ questionnaire, its validity and reliability native version were confirmed (validity, 96% reliability) and included 47 items in three subgroups of speech perception, spatial hearing, and auditory quality. Based on the results of the questionnaire, the mean score of each item and item of each index will be measured for the research participants.

*Rehabilitation training:* auditory rehabilitation was based on TFS. The intervention group will be asked to identify vowel consonant vowel words (VCVs) that have only TFS preserved and their envelope discarded. It is based on that VCVs that processing and converting to TFS speech. In this process the ENV of VCVs are eliminated and only TFS will be kept.

### Participants

Participants were recruited from elderly people, aged between 60 and 75 years old, referred to the audiology clinics of Iran University of Medical Sciences and were informed by phone about the study. They were selected based on previous clinical examination, including otoscopy, tympanometry and pure tone audiometry test (PTA) to identify type and level of a hearing loss. In a preliminary interview, speech perception difficulty was evaluated with a question if they had difficulty in understanding speech in noise. Those who respond yes were entered into the study. Later to define difficulty in understanding speech in noise we adapted questionnaire which was used by Tokgoz-Yilmaz
*et al*.
^25^.

We performed Mini Mental State Examination (MMSE) questionnaire in order to rule out prominent cognition difficulty in participants.

Participants were informed that can withdraw from the study at any time. Privacy concerning information and results of participants are respected.

The schematic diagram of study procedures is shown below
*Extended data:* Figure S1.

***Inclusion and exclusion criteria***.
*Inclusion criteria:* individuals with mild to moderate hearing loss and aged between 60–75 years, having diploma or higher degree; right-handedness (assessed using Edinburgh handedness inventory); speaking native language and being monolingual; complaint about speech in noise perception difficulties and normal condition of middle ear function.

*Exclusion criteria:* those who do not meet the inclusion criteria, unwillingness for participation in each step of study, conductive hearing loss and abnormal middle ear, central nervous system disease, head trauma, history of seizure attack and epilepsy, and use of psychiatric and nervous system drugs. Individuals with obvious cognitive problems, as diagnosed by Mini Mental State Examination (MMSE), were also excluded.

***Sample size***. The following formula is used to determine the number of samples in each group with the concern that the two groups are independent and dependent variables in this study are quantitative.
$$\text{n}=\frac{{\left(Z_{1-\frac{\text{α}}{2}}+Z_{1-\text{β}}\right)}^{2}({\sigma_{1}}^{2}+{\sigma_{2}}^{2})}{{\left({\text{μ}}_{1}-{\text{μ}}_{2}\right)}^{2}}$$

α1: standard deviation of the studied variable in the first group (case, exposed, or intervened)

α2: standard deviation of the studied variable in the second group (control, unexposed, or compared)

μ1: mean of the studied variable in the first group

μ2: mean of the studied variable in the second group

α=0.05

β=80%

Z= 1.96

Based on previous studies, a power of 85% and level of significance of 95% was determined for this study. We obtained a sample size of 15 individuals for each group (total = 30), which takes into consideration a 20% drop out.

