### Study design

The study will not involve complications for participants, but if there is extreme difficulty with cooperation for participants the test will be discontinued. All participants were informed both orally and in writing about the study process. Written consent to participant were obtained before the study start. There is no criteria for intervention modification in this study protocol. To improve adherence to intervention protocols, every training session the examiner provide feedback to all participants and inform them about the training progress. The rehabilitation sessions and duration are flexible for participant.

We randomly assigned participants in 1:1 ratio, intervention and control group. The intervention group undergo the rehabilitation training program.

The two groups were matched for age and gender. Those in the control group do not receive any rehabilitation programs during the study. The randomization was applied by random number table (those assigned an odd number, control group; those assigned an even number, intervention group).

***Study procedures***. Pre-rehabilitation, the SNR (50%) of all participants was measured using the word in noise (WIN) test. In addition, a binaural TFS test and the SSQ questionnaire score of all participants are evaluated (see section
*Outcomes* below).

***Rehabilitation training***. Participants identify the set of 16 consonants using one-interval forced-choice procedure and feedback with correct answer. On each test the participants select one of the stimuli from the set of 16 syllables. The participants are informed while the stimulus is presented that they should identify its middle consonant. Following each stimulus presentation, a 4 × 4 visual display of the response alternatives appear on a computer monitor and the participant select the response by using the computer mouse.

Each participant select a box, if they click the box correctly, the box turn green and if they choose the wrong answer, the box turn red. The participant is given visual feedback by showing the correct VCV with a yellow box. No time limit is be imposed on the participant's responses. Each experimental run consists of 64 trials derived from a different random-order presentation of the 64 syllables in the stimulus set. Each run is last 16 to 30 min depending on the participant's response time. The total duration of rehabilitation sessions are e five weeks. Experiments are controlled by a desktop PC.

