### Speech stimulus process

The TFS speech consists of single syllable recorded in / a / C / a / with various 16 consonant format which included Aja, Aka, Ara,…. and it is pronounced by a native-speaking man. The analogue signals are converted to digital a 16-bit at 44.1 KHz sampling frequency. The stimulus synthesis process is performed in MATLAB software and the software is provided in C programming language.

The original bandpass is filtered into 16 bands of equal bandwidth on a log frequency scale spanning 80 to 8020 Hz. Each Bandpass signal is decomposed to ENV and TFS by Hilbert transform. The ENV component is discarded and TFS component is normalized and TFS component in each band summed lastly creating TFS speech.

After rehabilitation, the SNR (50%) using the WIN test, and a binaural TFS test and SSQ questionnaire will be evaluated again in intervention group. Results will be compared in intervention and control groups before and after the rehabilitation program.

***Outcomes***.
*SNR (50%):* single syllable words in the presence of noise at different signal-to-noise ratios (0, + 4, + 8, + 12, + 16, + 20, + 24) as binaural in two study groups and compare the SNR (50%). Differences in scores before and after rehabilitation training between the two groups will be compared.

The Words-in-Noise (WIN) materials were developed to evaluate the ability of listeners to understand words in multitalker babble. The WIN involves in which the level of the noise is fixed and five words are presented at seven signal-to-noise ratios from 24 to 0 dB in 4 dB decrements. The 35 words are spoken by a native male speaker. The metric of interest is the signal-to-noise ratio (S/N) at which recognition performance is 50%, which is a value determined with the Spearman Karber equation see (
*Extended data:* S2).

Binaural TFS test: determines the binaural change of phase difference at different frequencies in intervention and control groups before and after rehabilitation training.

The correlation between the results of speech perception test scores in the presence of noise with the results of binaural TFS test in the two groups after rehabilitation program will be assessed.

*SSQ questionnaire score:* provided to each group before and after rehabilitation training. Scores between intervention and control groups will be compared (
*Extended data:* S3).

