## Discussion

Elderly populations are growing rapidly worldwide, and this higher number of older individuals is associated with an increase in prevalence and incidence of age-related disorders. Age-related hearing loss (presbycusis) is one the most common disorders with an increase in age. Hearing loss has significant negative impact in quality of life in elderly population. It causes limitation of communication and social activity
^1^.

Speech perception in noisy environments is very serious difficulty with presbycusis, The presbycusis is known as damage of hair cells in cochlea
^5^. The hair cells damage with presbycusis mostly associated with deteriorate of temporal fine structure (TFS) information
^7^.

TFS is important when background sounds are present
^9^. Loss of speech perception in noisy environments with presbycusis is mostly caused by damage of processing of TFS information. Our study is based on improvment of TFS deficit in cochlea.

The rehabilitation training is based on identify vowel consonant vowel words (VCV). 

The test is performed in several sessions. The total time of test is three times every week for total fives week for all subjects but the time in every session is different between participants.

To evaluate the efficiency of rehabilitation training we used temporal fine structure sensitivity test (TFS test), Speech in noise test (SNR 50%) and Speech, Spatial and Qualities of Hearing Scale (SSQ) 

They are performed in both intervention and control group but at the end of study we measure only the tests in intervention population.

Initially TFS1 was developed by Moore and Sek (2009) in order to discriminate a harmonic complex tone from the same tones with all components shifted upwards by the same amount in hertz leading to an inharmonic tone. The TFS-LF was described by Moore and Hopkins (2010) to measuring thresholds for detecting changes in interaural phase difference ( IPD). Although the TFS-LF is used generally but it has a limitation. The frequency of the tones is fixed, for example at 250, 500 or 750 Hz and some old

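### The exclusion criterion on unwillingness is not limited to the time before allocation, so it can remove randomised participants unequally by arm

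*Protocol article*

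**What the plan says.** In the protocol article, the exclusion criteria under Participants include "unwillingness for participation in each step of study". The items beside it (conductive loss and middle-ear abnormality, neurological history, drug use, cognitive screening) are judged once, at entry. This one refers to every step and gives no cut-off at allocation.

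Three other statements bear on it:

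- Participants also says: "Participants were informed that can withdraw from the study at any time". This applies to both arms.
- Study design says that "if there is extreme difficulty with cooperation for participants the test will be discontinued". What is discontinued is the test. The sentence does not say that the person leaves the trial or the analysis.
- The arms differ in what is asked of them after allocation. The Abstract gives the intervention group "30-minute sessions three times a week for a total five weeks". For controls, Study design says: "Those in the control group do not receive any rehabilitation programs during the study".

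The article is not consistent on whether controls have a final assessment. The outcomes text within Speech stimulus process says the SSQ is "provided to each group before and after rehabilitation training", whereas the Discussion says that "at the end of study we measure only the tests in intervention population".

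The sample size is 15 per group, "which takes into consideration a 20% drop out". That allowance is a single figure, not split by arm.

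**The concern.** An exclusion criterion that still operates after randomisation turns a post-randomisation event, refusing a session, into ineligibility. Here the opportunity for that event is unequal by design. A trainee who will not continue in the second week meets the criterion as worded. A control with the same hearing and the same tolerance has no session to refuse and stays.

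The people removed are unlikely to be a random subset. The article's hypothesis (Study overview) is that inability to use TFS cues is the main cause of poor speech perception in noise, and the training presents syllables with only TFS preserved. Those who find it intolerable could well include those who would score worst on the outcome. If they are excluded and not tested, the remaining trainees are a selected group, and training can look better than it is. The trial would also lose information on who could not complete training and why. With 15 per arm, two or three such exclusions matter, and no later analysis can recover final tests that were never taken.

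**Working it through.** **Exposure by arm.** Training arm: 3 sessions × 5 weeks = 15 occasions after allocation on which a participant may refuse. Control arm: 0 sessions, plus one final assessment under the outcomes text or none under the Discussion. On either version the criterion has far more room to act in the training arm.

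**The plan's own figure.** The means and SDs behind 15 per group are not given, so the figure cannot be reproduced from the printed formula. It does fit 12 evaluable per group, since 12 / (1 − 0.20) = 15. Solving the formula for the standardised difference with n = 12, two-sided α = 0.05 and 85% power gives d = √(2/12) × (1.96 + 1.036) = 1.22. At 80% power it is 1.14. Twenty per cent of 15 is 3.

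**Illustration of bias.** These are assumptions, not protocol figures. There is no true effect, outcomes are standard normal and scored so that higher is better, and there are 15 per arm. The 3 trainees lowest on a latent tolerance score are removed, and no controls are. Tolerance has correlation ρ with outcome, and the test is an unadjusted two-sided t-test at 5%. The expected bias is ρ × m, where m is the mean of the upper 12 of 15 standard normal values. Simulation gives m = 0.328 (large-sample check: φ(−0.84)/0.8 = 0.35). So 0.3 × 0.328 = 0.098 and 0.5 × 0.328 = 0.164. Simulation with 100,000 runs per case gave:

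| ρ | Bias (SD) | Two-sided type I error | False positives favouring training (nominal 2.5%) |
|---|---|---|---|
| −0.5 | −0.16 | 7.3% | 1.0% |
| 0 | 0.00 | 5.1% | 2.5% |
| 0.3 | +0.10 | 5.8% | 4.4% |
| 0.5 | +0.16 | 7.1% | 6.2% |
| 1 | +0.33 | 15.8% | 15.4% |

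At ρ = 0.5, removing 1, 2, 3 or 4 trainees gives +0.06, +0.12, +0.16 and +0.21 SD, with type I error of 5.5%, 6.4%, 7.1% and 8.4%. Removing 3 from each arm by the same mechanism gives no bias, so the asymmetry between the arms is what matters.

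**With baseline adjustment.** Analysis of covariance is named under Statistical analysis, so the same loss was examined with the baseline score as covariate, assuming a baseline–outcome correlation r of 0.5 or 0.7.

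- Loss driven only by baseline: ANCOVA bias is about 0.00 SD and rejection about 5%. The unadjusted t-test on the same data shows 0.11 to 0.24 SD.
- Loss also related to outcome beyond baseline (assumed correlation 0.5 with the residual): the bias is about 0.5 × √(1 − r²) × 0.328. That is 0.5 × 0.866 × 0.328 = 0.14 SD for r = 0.5 and 0.5 × 0.714 × 0.328 = 0.12 SD for r = 0.7. Simulated values across such cases were about 0.11 to 0.15 SD, with type I error near 7%.

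**Relative size.** At ρ = 0.5 the unadjusted bias is 0.16 / 1.22 = 13% of the difference implied by the sample size.

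**The case against.** The phrase sits in an eligibility list, and Study status says that enrolment is complete while allocation is still to come. It may therefore mean only that people unwilling to undertake all study steps were not enrolled. Sessions are flexible and feedback is given at each one to support adherence, which should keep refusals few. All this is fair, and it limits how often the criterion would bite. It does not change the wording: unwillingness at a training step can only appear after allocation, and the criterion covers each step.

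Three stronger readings are tempting, and the document supports none of them.

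- A reader might infer that uncooperative participants are discontinued from the trial. Study design discontinues the test. The article uses that word both for training (Discussion) and for the outcome measures, and nowhere says that the person is removed.
- A reader might infer that people are in fact removed almost only from the training arm. No figures by arm are given, controls may also withdraw, and the 20% allowance is not split.
- A reader might infer a definite bias towards training. That needs those removed to have worse outcomes and their data to be left out. The bias is zero if loss is unrelated to outcome, and it reverses if those lost would have done better.

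Baseline adjustment is the best statistical defence and largely answers the case where loss reflects baseline ability alone. It does not answer loss related to outcome beyond baseline. The article also names ANCOVA beside a paired t-test, to be chosen according to circumstances, so it is not a firm commitment.

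Finally, the absence of a stated analysis population is not the point, since a full protocol or SAP may supply one. The point is a stated criterion that is badly bounded.

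**Conclusion.** The concern holds as a fault of wording with a design consequence. As written, the criterion can exclude randomised participants, and the opportunity is concentrated in the training arm. The likely direction favours training but is not established.

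If 3 of 15 were lost from training only and there were no true effect, an unadjusted comparison would show about 0.10 to 0.16 SD of spurious benefit and 6 to 7% type I error at correlations of 0.3 to 0.5. The figure of 0.33 SD with about 15% is an upper extreme that needs perfect correlation. With ANCOVA the range runs from about zero, if loss depends on baseline only, to about 0.11 to 0.15 SD under the assumed residual correlation of 0.5. The number lost, its confinement to one arm and the correlations are all assumptions. The distortion is modest under the middle assumptions, but it is avoidable, and it should be corrected.

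**What to change.** 1. Under Participants, limit the criterion to unwillingness expressed before allocation.
2. Under Study design, state that a participant who stops training for any reason stays in the study unless consent is withdrawn, is invited to the final WIN, TFS-LF and SSQ tests, and is analysed in the assigned group. Report by arm how many stopped and why.
3. Leave the discontinuation rule as it stands, and make clear only that discontinuing the test is not removal from the trial.
4. Reconcile the outcomes text and the Discussion on whether controls have the final tests, because keeping everyone in the comparison presupposes that both arms are tested.

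The cost is a few sentences in an amendment and, at the plan's own 20%, about three extra invitations to final testing. Including people who stopped training may dilute the estimated effect slightly; a completers analysis can be shown as secondary. On the Study status account allocation has not yet taken place, so the change can be made beforehand. Study design, however, describes assignment in the past tense. If allocation has already been done, the change should be dated and made before final testing.

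### The sample-size paragraph gives conflicting power inputs (beta of 80% against power of 85%) and no outcome, means or SDs, so 15 per group cannot be reproduced

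*Protocol article*

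**What the plan says.** The Sample size paragraph, under Participants, introduces a two-means formula: "The following formula is used to determine the number of samples in each group with the concern that the two groups are independent". The formula contains Z at 1 − α/2 and Z at 1 − β. The legend then gives α = 0.05, β = 80% and Z = 1.96.

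The means and SDs appear only as definitions, for example "mean of the studied variable in the first group" and "standard deviation of the studied variable in the first group (case, exposed, or intervened". No values follow, and the variable studied is not named. The Outcomes section lists the SNR (50%), the binaural TFS test and the SSQ score, and does not say which of them sized the trial.

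The closing text reads: "Based on previous studies, a power of 85% and level of significance of 95% was determined for this study". The result is: "We obtained a sample size of 15 individuals for each group (total = 30), which takes into consideration a 20% drop out". Allocation is 1:1 (Study design).

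**The concern.** The formula takes Z at 1 − β, so β is the type II error rate and power is 1 − β. A β of 80% and a power of 85% cannot both be the input. A significance level of 95% also does not fit α = 0.05 as written.

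The stated power tells a reader what size of effect the trial was built to find, and how much weight a non-significant result can bear. Here that figure cannot be traced. Two different powers are printed, and the quantities that would show which one was used (outcome, means, SDs, n before dropout) are absent.

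**Working it through.** **Inputs from the protocol.** α = 0.05 two-sided (Z = 1.96); β = 80% in the legend; power 85% in the text; 15 per group including 20% dropout; 1:1 allocation. Means and SDs are not given, so the standardised difference d = (μ1 − μ2)/σ, taking equal SDs, is unknown. Every d below is back-solved or assumed.

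**Can the plan's figure be reproduced?** Not forwards, because d is missing. Backwards, 15 × 0.8 = 12 evaluable per group. With equal SDs the formula is n = 2(Z₁₋α/₂ + Z₁₋β)²/d².

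**What each reading of the power input gives.**

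| Reading | Z₁₋β | 2(1.960 + Z₁₋β)² | d implied by n = 12 |
|---|---|---|---|
| β = 80% literally (power 20%) | −0.842 | 2.50 | 0.46 |
| β = 80% meaning power 80% | 0.842 | 15.70 | 1.144 |
| Power 85% | 1.036 | 17.96 | 1.223 |

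The last column is √(numerator/12), for example √(17.96/12) = 1.223.

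**Size of the conflict.** The ratio of n at 85% to n at 80% is 17.96/15.70 = 1.144, about 14% more. If 12 was obtained at 80% power, then d = 1.144, and 85% power at that d needs 17.96/1.144² = 13.7, so 14 evaluable. Then 14/0.8 = 17.5, so 18 randomised per group, against 15 planned.

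**Does 15 per group also follow at 85%?** Yes, for some d. At d = 1.25, 17.96/1.25² = 11.5, so 12, and 12/0.8 = 15. The formula's power with 12 evaluable is then 86.5%. Both powers can therefore lead to 15, and the result does not show which was used.

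**Check with the t distribution.** At 85% power the formula rounds up to 12 for d from √(17.96/12) = 1.223 to √(17.96/11) = 1.278. Noncentral-t power for an unadjusted two-sample t-test with 12 per group runs from 81.7% to 84.9% over that range. If the formula was run at 80%, d lies between 1.144 and √(15.70/11) = 1.195, and t-test power runs from about 76% to 79.9%. Solving for d with 12 per group gives 1.28 for 85% power and 1.20 for 80%.

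**The case against.** A reader might infer that 15 per group with 20% dropout fails to give 85% power under the plan's own formula. The document does not support this. Without means and SDs no failure can be shown, and the formula does give 85% with 12 evaluable per group once d is about 1.22 or more.

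The t-test shortfall in that case is at most about three percentage points. A normal-approximation formula is common practice, so this is a refinement and not an arithmetic error. It also assumes the full 20% loss and no baseline adjustment. With all 15 per group evaluable, t-test power at d = 1.22 is about 90%. The Statistical analysis section names analysis of covariance, and the SNR (50%) is measured in everyone before rehabilitation. If the SDs used were those of post-training scores, an assumed baseline correlation of 0.3 brings power at d = 1.22 with 12 per group back to about 85%, and 0.5 to about 91%.

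A reader might also suppose that 15 was the number before dropout, but the text says dropout is already included. The 20%-power reading is almost certainly a labelling slip. The 95% is plainly a confidence level, since α = 0.05 and Z = 1.96 stand beside it and the Statistical analysis section fixes 0.05 for all tests.

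All of this stands, and it limits the point. It does not remove the conflict: even on the kindest reading of β, 80% is not 85%.

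**Conclusion.** The concern holds in a limited form. The paragraph prints two incompatible power inputs, and the significance wording needs correcting. Because no outcome, means or SDs are given, 15 per group cannot be reproduced or assigned to either power. The realistic ambiguity is 80% against 85%: about 14% in n, or 15 against 18 randomised per group if the calculation was in fact run at 80%.

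Whether 85% is reached is undetermined. The plan's formula reaches it at d of about 1.22 or more. For the d values at which that formula returns 12 at 85% power, an unadjusted t-test has about 82% to 85%. These figures assume equal SDs and 12 evaluable per group. The t-test figures also assume no baseline adjustment.

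**What to change.** Keep 30 participants; the Study status section says enrolment has been performed. Rewrite the paragraph as follows:

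- State α = 0.05 two-sided and a single power value, with β = 1 − power. Remove the β of 80% and the significance level of 95%.
- Name the outcome that the calculation concerns. The SNR (50%) is the one that matches the stated aim.
- Give the μ1, μ2, σ1 and σ2 actually used, with their source, and n per group before and after the 20% dropout allowance.
- If the calculation was run at 80%, restate the power as 80%.
- Add that, with 12 evaluable per group and an unadjusted two-sample t-test, 85% power requires a difference of about 1.28 SD (about 1.20 SD for 80%), and that baseline adjustment by analysis of covariance may lower this.

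The cost is one rewritten paragraph, with no extra participants and no change of procedure. The drawback is that the stated power may become slightly less favourable.
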